[name] also has demonstrated that 25OHD levels are inversely associated with risk of respiratory infection and wheezing illness in New Zealand children.([name] CA Jr, Ingham T, Wickens K, Thadhani RI, Silvers KM, Epton MJ, Town GI, Espinola JA, Crane J. Cord blood 25-hydroxyvitamin D levels and risk of childhood wheeze in New Zealand. Am J Respir Crit Care Med 2008; in press) We propose to test the impact of the repletion strategies on the incidence of respiratory infections, including among children with asthma.

Academic attention: Teachers in the pilot study school volunteered in conversation that they felt that the children paid better attention during the milk intervention month. If true, this is probably due to the increased calories of the intervention. If we were to document improved attention with the milk intervention, this would be useful information for the Ministry of Education’s debate regarding school lunch programs. We will ask the classroom teachers to complete an evaluation of each student’s attentiveness and behavior before and after the intervention. We would also like to pilot test a translation of the computer-based Continuous Performance Test, commonly used to measure attentive focus.

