###### Specific Aims

The goals of this two-year project are to raise national awareness in Mongolia regarding the public health impact of widespread vitamin D deficiency, to improve Mongolian capacity to monitor and redress vitamin D deficiency, to strengthen research capacity, and to provide data on supplements and food fortification as alternative strategies to prevent vitamin D deficiency. To these ends, we will convene a national conference, set up a national vitamin D laboratory, and conduct an intervention trial. Having observed rapid linear growth in Mongolian children drinking fortified milk in our pilot study, we would also like to assess the impact of milk consumption on growth and plasma somatotropin levels. The three-month intervention trial will test the impact of vitamin D fortified milk and vitamin D supplements on plasma levels of vitamin D (25(OH)D), plasma somatotropin levels, short-term growth, and respiratory infections, asthma, and eczema in Mongolian prepubertal children. Teachers will complete a Classroom Behavior Checklist for each child before and after the intervention, so that we can compare the impact of the interventions on classroom attention and behavior. We would also like to adapt and test the Continuous Performance Test (CPT) of attention in a subgroup of the students to document the (presumed increase) in attention that we expect to come from improved nutrition.

The aims of the intervention trial are:

Specific Aim 1: To measure the prevalence in winter of vitamin D deficiency among Mongolian schoolchildren and to compare the impact on plasma 25-hydroxyvitamin D (25(OH)D levels of two vitamin D supplement regimens and vitamin D fortified milk. Specifically, we hypothesize that after three months of intervention from January to March:

1. Daily vitamin D supplements of 300 IU will yield higher levels of 25(OH)D than will monthly supplements of 6000 IU.
2. Daily consumption of milk fortified with 300 IU will yield higher levels of 25(OH)D than will either supplement regimen.
3. Supplementation and fortification will each yield higher levels of 25(OH)D than consumption of unfortified milk.

Specific Aim 2: To test the impact of various types of milk on childhood plasma somatotropin levels and growth. Specifically, we hypothesize that:

1. Daily consumption of cow’s milk will yield higher levels of growth hormone, IGF-1, and IGF-1/IGFBP3 than will daily consumption of equivalent nutrients in a milk substitute.

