1. Recruitment: In collaboration with the Health Sciences University of Mongolia, we propose to recruit 750 girls and boys in 3rd grade from 10 Ulaanbaatar public schools. The children will be 9-11 years old.

2. School selection: School selection will consider the following factors: socioeconomic position; geographic location; school size; current lunch or supplementation program; and the interest and willingness to participate of the school’s administration and faculty. [name] will travel to Mongolia in May 2008 to visit schools and talk to officials about possible participation. We will get written documentation from principals of schools who agree to participate.

3. Eligibility: Children will be eligible to participate if they report no known allergies to milk, nuts, coconut, or wheat.

Study Design

1. Six-arm randomized partially-blinded feeding intervention study to test the impact of vitamin D supplements and fortified cow’s milk on the plasma 25(OH)D, growth hormone, and IGF-1 of prepubertal children. As detailed below, the arms include: monthly vitamin D supplements (n=100); daily vitamin D supplements (n=100); daily fortified U.S. cow’s milk (n=150); daily fortified Mongolian cow’s milk (n=150); daily fortified milk substitute (n=150); and daily unfortified Mongolian milk (n=100).

2. The intervention will run for three months, from January 2009 through March 2009, to coincide with the darkest months of the year. There will be a two-week break in the intervention to coincide with the school holiday in February. (It is highly unlikely that children would leave Mongolia during this period, so there are no concerns about increased sunlight exposure over vacation.)

3. Study measures will include: height, sitting height, weight, grip strength, asthma, eczema, respiratory illness, and (at baseline only) clinical signs of rickets and Tanner stage (sexual maturity). An 8 ml blood sample will be drawn at baseline and at the conclusion of the intervention. Classroom attentiveness and behavior will be rated by the classroom teacher for each child at the beginning and end of the intervention. A subset of children will perform the Continuous Performance Test as a pilot.

Intervention

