Blood samples will be collected and cooled immediately before transportation to the Health Sciences University of Mongolia Laboratory, where they will be spun, aliquotted into 4 x 1ml cryotubes, and frozen. White cells (DNA) will be discarded. To guard against freezer failure, one set of aliquots will be kept in the electrical -70 freezer (with generator backup) at the HSUM laboratory, and the other set in a liquid nitrogen -80 freezer at the laboratory of [name], with whom we collaborated for the pilot study. Assays will be run in Canada, and will require shipment by express carrier on dry ice. We accomplished this during the pilot study, and are seeking even faster methods with the cooperation of Korean Air and courier services.

1. **Trained medical student volunteers will measure height, sitting height, weight, and grip strength at both baseline and at the conclusion of the study.** Trained medical volunteers will assess Tanner stage and rickets symptoms at baseline only.
2. Trained medical student volunteers will perform a dermatologic exam to derive Investigator Global AD Assessment (IGADA) and EASI score at both baseline and at the conclusion of the study.
3. Classroom teachers will complete the Classroom Behavior Questionnaire for each child at the beginning and end of the study. For a subset of students, trained medical student volunteers will perform the Continuous Performance Test with children at baseline and at the conclusion of the study. (The computer will generate dot matrix numbers (3..6..2..8..1..10..) that will appear on the CPT screen. The child will be asked to push a response button each time they see the target stimulus preceded by a certain number appear on the screen. The task should take approximately 15 minutes.)
4. **The first week of the milk intervention will be a ‘phase-in’ period, in which 236 ml/per day of milk or milk substitute will be consumed for the first three days, followed by 472 ml/per day over the next two days**. **In the second week, the full 710 ml protocol will be initiated**. The vitamin D supplement arms will be phased in accordingly (100 IU days 1-3, 200 IU day s 4-5; 300 IU thereafter for the daily supplement arm; 5200 IU will be given for the first monthly dose for those in the monthly supplement arm. See schedule in table 1.

Table 1. Schedule of vitamin D fortification/supplementation

|  | Schooldays | Daily IU in daily supplement and fortified milk arms | Monthly IU in monthly supplement arm |

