4. 300 IU in 710 ml on schooldays of milk ‘substitute’ that has the same macronutrient and very nearly the same micronutrient content as cow’s milk. (n=150) The substitute is a vegetable-based macronutrient substitute for milk. It consists of: almond milk (Pacific); coconut milk (Taste of Thai); and wheat gluten (King Arthur). A non-nutritive thickener (Simply Thick) made from xantham gum is added to give the consistency of whole milk. The Pacific almond milk is fortified with calcium and vitamin D. The recipe is found in Appendix 11.
5. 300 IU vitamin D supplements on schooldays (n=100). (the first month will follow the following schedule to parallel the milk “phase-in: 100 IU/day for three days; 200 IU/day for two days; 300 IU/day thereafter)
6. Larger dose vitamin D supplements once a month (n=100). The maximum daily dose of the “monthly supplement” will be 2000 IU, per Institute of Medicine upper limits for children.[Standing Committee on the Scientific Evaluation of Dietary Reference Intakes FaNB, Institute of Medicine: Dietary Reference Intakes for Calcium, Phosphorus, Magnesium, Vitamin D, and Fluoride. National Academy Press, Washington, D.C., 1997. <http://books.nap.edu/openbook.php?record_id=5776&page=285> ] The “monthly dose” will in fact be spread over several days at the start of each month. (See table 1, in Section L.3C.7 above, for the detailed schedule.)

With the exception of the unfortified milk arm (arm #3), all arms will get 14,200 IU of vitamin D over the three months. Parents of children in the unfortified milk arm will receive an equivalent amount of vitamin D supplements at the conclusion of the trial.

We will use vitamin D tablets produced by Nature Made.

Randomization method for intervention and control groups:

We will use a mix of block and individual-level randomization. Some children will receive supplements (1 of 2 supplement regimens), while other children will receive milks (one of 4 milks). Since the milk is more desirable to children than supplements, it would be unacceptable to randomize children in the same classroom to milk or supplement. However, we think it is acceptable to have one classroom in a school be a supplement classroom, and the other a milk classroom. We do this to minimize socioeconomic confounding; our primary concern here is having equivalent baseline nutritional status across intervention arms.

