3. In deference to issues raised by the Mongolian ERB, we have eliminated the Tanner examination by the trained medical students. Instead, we will ask the children to complete a pencil-and-paper questionnaire (attached) which has been used by children in other studies (notably, the Growing Up Today Study) to indicate their level of pubertal development. We feel it is necessary to include some assessment of pubertal development, due to the study’s intention to measure growth. It is important to understand where in their growth spurt that children might be, and the best way we know to assess this is to have some measure of pubertal development. The ERB also suggested that the Child Evaluation Form has too many open-ended questions. We have added response choices to most of the questions.

4. We propose to supplement the Cognitive Performance Test with a 5-minute processing speed subtest of the Wechsler Intelligence Scale for Children (WISC). The test will be administered at the beginning and end of the study to see whether the nutrients provided in the milk improve children’s cognitive performance over three months.

5. We have replaced the more intensive dermatologic examination with a more simple self-report and examination of flexural dermatitis (dermatitis at skin creases, such as elbows and knees), better suited to trained medical student administration

6. Urine assay: We propose to test first morning urine void urines using the “whizpop” (pee-on-a sponge) collection kit, which we have used successfully with 6-8 year olds in Boston. The children will be given the collection kit to take home. They will test for three sequential days at the start of the study and three at the conclusion. We have added first morning urine samples because we have colleagues who report being close to developing urine-based growth hormone assays. Since growth hormone is highly variable, use of three measures at baseline and three at trial completion would provide a more stable estimate of change in growth hormone due to the intervention. Measurement of growth hormone is a primary aim of this study, so we are hopeful that the assay development will be successful. At present, we do not have a budget to cover these assays, but will seek funds if the assay development is successful.

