**AMENDMENT #3**

**In our original application, we proposed to enroll students from 10 different schools to ensure that this would allow us to enroll a total of 750 children in the study. During our September visit, we discovered that some of our targeted schools have gown rapidly as a result of increases in area populations due to immigration from the countryside. This influx of students allows us to recruit children from two schools, rather than 10. We decided to adopt this change due to budget constraints and logistic considerations.**

We have recently learned that the school vacation schedule we were originally given by the Ministry of Education is not correct for the two schools (#62 and #65) from which we will recruit students. Instead of a one week February break, the children will have vacation from January 17-25 and March 22- April 5. We had originally planned to run the intervention from January 19 through the end of March, on schooldays only. **We have regrouped with our Mongolian colleagues and the schools to change the schedule to fit the intervention in between the two vacations: from January 26-March 20, including weekends.** (During our pilot study in School #65 in 2005, the intervention was daily, including weekends).

The children in the milk arms will receive milk daily (a total of 300 IU), and children in the daily vitamin D dose arms will receive 300 IU supplements daily (instead of 5 days per week). **The intervention will still run the same total number of days.**

The children in the ‘monthly dose’ group were originally intended to receive between 1000-2000 IU over 3 days at the beginning of each month, for a total of 15000 IU over three months, the equivalent vitamin D dose as the milk and daily supplement groups. The intention was to compare the effectiveness of a once monthly supplement (easier to administer from a public health standpoint) to a once daily supplement. So that we can measure plasma vitamin D levels in the ‘monthly’ group at their nadir, we planned to draw the plasma at about 30 days after the last monthly dose.

Now that we are compressing the daily milk and daily supplement intervention into approximately 50 days instead of three months by including weekends, we also need to deliver the ‘monthly’ dose in approximately 50 days. We propose to do this by giving the children 1700-2000 IU per day for 7 days at the beginning of the trial.

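### The teacher-rated attention checklist cannot give an unbiased milk-versus-supplement comparison, because each teacher rates only one side of it and can see which

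*Supplement*

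**What the plan says.** All references are to the Fortification Study protocol summary unless stated.

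- **Rater.** Study Design: "Classroom attentiveness and behavior will be rated by the classroom teacher for each child at the beginning and end of the intervention". The introduction to the Specific Aims gives the purpose: "Teachers will complete a Classroom Behavior Checklist for each child before and after the intervention, so that we can compare the impact" on classroom attention and behaviour.
- **Question.** Background, Academic attention, reports that teachers in the pilot school volunteered that "they felt that the children paid better attention during the milk intervention month". It adds: "If true, this is probably due to the increased calories of the intervention". The result is meant to inform the Ministry of Education's school-lunch debate.
- **Allocation.** Under the randomization method, "it would be unacceptable to randomize children in the same classroom to milk or supplement", so each class is either a milk class or a supplement class. Within a milk class, children are randomized among the four milk products. Within a supplement class, they are randomized between daily and monthly supplements.
- **Visibility.** A milk monitor hands out product in the classroom and watches it being consumed. Class type is fixed before the introductory meetings, and consent is specific to it. The trial is described as partially blinded. No masking of teachers and no independent rater is mentioned.
- **Other attention measures.** Intervention section: "For a subset of students, trained medical student volunteers will perform the Continuous Performance Test" (CPT) at baseline and at the end. Amendment 1, item 4: "We propose to supplement the Cognitive Performance Test with a 5-minute processing speed subtest" of the WISC, also at both times.
- **Schools.** Amendment 3 reduces ten schools to two, #62 and #65, and notes: "During our pilot study in School #65 in 2005, the intervention was daily, including weekends". It does not withdraw the rule against mixing milk and supplement in a class.

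**The concern.** The attention question in the Background is about the calories that milk adds. The milk products cannot answer it among themselves: the substitute was designed to have the same macronutrients as cow's milk, and Amendment 2 adds crackers so that the milk arms are comparable in carbohydrates and calories. Only children in supplement classes go without those calories, so only milk versus supplement addresses the question.

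On the checklist, that contrast coincides with the rater. A teacher who expects milk to help may score the class more kindly at the end, and nothing in the ratings distinguishes this from a real gain. There is documented reason to expect such a belief: the remarks at the pilot school, and the investigators' own reference to a presumed increase in attention. The risk is that teacher opinion reaches the Ministry as trial evidence for a school milk programme.

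**Working it through.** The documents give no sample size, effect size or named test for attention, so there is no stated figure to reproduce. The check has two parts.

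**1. Can the milk effect be separated from the teacher?**

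For child *i* of teacher *j*, write the end-minus-baseline rating as

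change = β·milk(j) + shift(j) + error,

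where shift(j) is the change in that teacher's scoring between the two ratings.

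- A teacher's constant severity is in both ratings and cancels in the difference. A shift between ratings does not cancel.
- milk(j) is the same for every child of a teacher. It therefore equals the sum of the indicators of the milk-class teachers, and adding it to a full set of teacher indicators adds no rank. This holds for any number of classes. As an illustration, with 20 classes (the layout drawn before Amendment 3) the rank is 20 with or without the milk term.
- An indicator for milk type within a class raises that rank to 21, so within-class contrasts can be estimated with the teacher held constant.
- A classroom random effect treats shift(j) as varying around a common mean. If milk teachers have mean shift a and supplement teachers mean shift b, the estimate is centred on β + (a − b). The random effect widens the standard error but leaves (a − b) in place.

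Randomizing classes does not help, because the shift arises after assignment.

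**2. How much could it matter?**

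Inputs from Study Design: supplement arms 100 + 100 = 200 children; milk arms 150 + 150 + 150 + 100 = 550. Assumptions not in the documents: no true effect, SD of change 1, a difference in shift (a − b) of 0.1 to 0.3 SD, and, where clustering is allowed for, 40 children per class and an ICC of 0.10.

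- Ignoring classrooms: SE = √(1/200 + 1/550) = 0.0826. Difference detectable with 80% power = 2.8 × 0.0826 = 0.23 SD.
- Allowing for classrooms: design effect = 1 + 39 × 0.10 = 4.9. SE = 0.0826 × √4.9 = 0.183. Detectable difference = 2.8 × 0.183 = 0.51 SD.

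Chance of a significant result = 1 − Φ(1.96 − (a − b)/SE) + Φ(−1.96 − (a − b)/SE):

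| Difference in shift (assumed) | Classrooms ignored | Clustering allowed for, ICC 0.10 |
|---|---|---|
| 0 | 5% | 5% |
| 0.1 SD | 23% | 8% |
| 0.2 SD | 68% | 19% |
| 0.3 SD | 95% | 37% |

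In both columns the bias in the estimate equals the assumed shift. Clustering changes only how often that bias is declared significant. With about 500 milk children, as the randomization section has it, the first detectable difference is 2.8 × √(1/200 + 1/500) = 0.23 SD, so the choice makes no material difference.

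**The case against.** **Attention is peripheral.** None of the four Specific Aims names it. It is absent from the primary and secondary comparisons, from Table 4 and from the later analysis plan. The stated purpose of comparing interventions also covers milk types and daily versus monthly supplements, where one teacher rates both sides. This stands, and it limits the importance of the point. The Background nevertheless ties the result to a policy debate about milk, so a milk-versus-supplement reading of the checklist is foreseeable and nothing excludes it.

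**Measures that do not depend on the teacher are already planned.** The CPT and the processing-speed subtest are in the protocol as amended. Medical students perform the CPT, while separate milk monitors distribute product. This also stands. A reader might infer that milk's effect on attention rests on teachers alone and cannot be studied in this trial; the documents do not support that. However, the CPT is a pilot in a subset of unstated size. For neither test is a milk-versus-supplement comparison or masking of testers described.

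**The evidence of expectation is thin.** The remarks were conversational, and nothing shows that the same teachers would rate in this trial. Supplement teachers could also expect a benefit, and only the difference between the two groups biases the contrast. This is fair: the direction is plausible but the size is unknown.

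**Significance depends on the analysis.** The protocol's general tool is a simple t-test, but the later plan uses classroom random effects for other outcomes. The second column of the table shows how much this matters.

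**Conclusion.** The point holds for one use of one instrument: the teacher checklist as evidence on milk versus supplement. In that use the treatment effect is fully confounded with a rater who is very probably unmasked, and no analysis of the ratings can undo it. The bias equals the difference in mean end-of-study shift between milk and supplement teachers, whatever that is.

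The conclusion rests on two inferences: that teachers know their class type, which 710 ml of milk against tablets given in class makes hard to doubt, and that each class is rated by its own teacher.

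Three stronger readings are not supported:

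- A spurious effect of a particular size cannot be claimed, because every shift in the table is an assumption.
- The contrast cannot be described as about 5 supplement teachers against 13 to 15 milk teachers. Those counts belong to the ten-school layout, and none are given for the two schools.
- The vitamin D, somatotropin and growth results do not depend on teacher ratings and are untouched.

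**What to change.** 1. State that the checklist will be compared only between arms within the same classroom (milk types; daily versus monthly supplement) and will not be used as evidence for milk versus supplement. This holds the rater constant. A teacher may still notice which child takes which product, so the within-class result should also be read with care.
2. Base any milk-versus-supplement statement on attention on the CPT and the processing-speed subtest. Draw the children already planned for testing from milk and supplement classrooms in both schools, and do not tell the medical-student testers the classroom's assignment.
3. Allow for classroom in that comparison, since class is the unit assigned, and label the result exploratory.

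The change is to wording, to the choice of tested children and to tester instructions; it calls for no new test. The cost is precision: the tested subset is smaller than the full sample and its size is not stated. If it proves too small to be useful, the choice is between enlarging it, which would take more testing time, and making no milk-versus-supplement claim on attention.
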